## Abstract

**Background:**

Community-acquired pneumonia is an important cause of morbidity and mortality in adults. Approximately one-third of pneumonia cases can be attributed to the pneumococcus. Pneumococcal conjugate vaccines (PCVs) protect against colonisation with vaccine-type serotypes. The resulting decrease in transmission of vaccine serotypes leads to large indirect effects. There are limited data from developing countries demonstrating the impact of childhood PCV immunisation on adult pneumonia. There are also insufficient data available on the burden and severity of all-cause pneumonia and respiratory syncytial virus (RSV) in adults from low resource countries. There is currently no recommendation for adult pneumococcal vaccination with either pneumococcal polysaccharide vaccine or PCVs in Mongolia. We describe the protocol developed to evaluate the association between childhood 13-valent PCV (PCV13) vaccination and trends in adult pneumonia.

**Methods:**

PCV13 was introduced into the routine childhood immunisation schedule in Mongolia in a phased manner from 2016. In March 2019 we initiated active hospital-based surveillance for adult pneumonia, with the primary objective of evaluating trends in severe hospitalised clinical pneumonia incidence in adults 18 years and older in four districts of Ulaanbaatar. Secondary objectives include measuring the association between PCV13 introduction and trends in all clinically-defined pneumonia, radiologically-confirmed pneumonia, nasopharyngeal carriage of *S. pneumoniae* and pneumonia associated with RSV or influenza. Clinical questionnaires, nasopharyngeal swabs, urine samples and chest radiographs were collected from enrolled patients. Retrospective administrative and clinical data were collected for all respiratory disease-related admissions from January 2015 to February 2019.

**Discussion:**

Establishing a robust adult surveillance system may be an important component of monitoring the indirect impact of PCVs within a country. Monitoring indirect impact of childhood PCV13 vaccination on adult pneumonia provides additional data on the full public health impact of the vaccine, which has implications for vaccine efficiency and cost-effectiveness. Adult surveillance in Mongolia will contribute to the limited evidence available on the burden of pneumococcal pneumonia among adults in low- and middle-income countries, particularly in the Asia-Pacific region. In addition, it is one of the few examples of implementing prospective, population-based pneumonia surveillance to evaluate the indirect impact of PCVs in a resource-limited setting.

## Background

Adult community-acquired pneumonia (CAP) is an important cause of morbidity and mortality, especially in high-risk groups, both in high- and low-income countries. The burden of pneumococcal pneumonia among adults is not well characterised. Historical estimates were generally based on blood culture results only and therefore underestimated true disease burden [1], or included sputum which may reflect carriage and therefore overestimated burden [2]. Two luminex platform-based multiplex serotype-specific urinary antigen detection (SSUAD) assays have been developed and validated for identification of key *S. pneumoniae* serotypes in urine samples from adults with radiologically-confirmed CAP, which may assist in defining the burden of non-bacteraemic pneumonia [3, 4]. A meta-analysis that included studies utilising additional diagnostics such as the BinaxNOW® *Streptococcus pneumoniae* urine antigen test, attributed 27% of adult CAP to the pneumococcus [1]. This analysis, however, mainly included studies from high-income countries.

Nasopharyngeal pneumococcal carriage is a precursor to pneumococcal disease [5]. Pneumococcal conjugate vaccines (PCVs) protect against colonisation acquisition or density with vaccine-type (VT) and potentially some cross-reactive serotypes, while overall pneumococcal carriage prevalence is only slightly decreased (or unchanged) due to serotype replacement [6]. Nevertheless, reductions in transmission of VT serotypes have resulted in large indirect effects in high-income settings [7] because VTs tend to be more likely to cause disease than replacement serotypes. Indirect or “herd” effects of vaccines refer to the indirect protection of the non-vaccinated population with a reduction in disease or carriage within this group [8].

There are limited systematic data from developing countries demonstrating the indirect impact of childhood pneumococcal vaccination on adult pneumonia and results from developed countries cannot necessarily be extrapolated to developing countries [9]. For example, there is more frequent pneumococcal carriage in low- and middle-income countries with horizontal transmission between children and adults; developing country PCV schedules often do not include a post infancy booster dose (which may be critical to reductions in transmission) [10]; crowding and other factors may influence carriage density [11, 12]; indoor and outdoor pollution may damage upper airway mucosa [13] which may also then influence pneumococcal carriage; and transmission pathways may differ by geography such as the potential for serotype 1 transmission outside of early childhood in the African meningitis belt [14]. One of the few studies in a resource poor setting [15] – from Kenya – reported a 47 to 94% reduction in adult pneumococcal pneumonia incidence following the introduction of the 10-valent PCV using a 3 + 0 schedule (6,10 and 14 weeks) in the childhood immunisation programme. Even though other improvements in healthcare may have contributed to the decline, the authors argued that the indirect PCV effect could have a considerable effect on adult disease in a high burden setting [15]. While encouraging, these data need to be replicated in other settings. Because of the high burden of pneumococcal pneumonia outside of childhood, particularly among older adults and those with underlying cardiac and respiratory diseases, results will have importance for immunisation policies, including use of infant booster doses and the vaccination of older and other high-risk adults.

Viruses and pneumococci in the upper airway may interact to lead to a viral, pneumococcal or combined lower respiratory infection [16]. For example, many deaths during the 1918 influenza pandemic were attributed to secondary pneumococcal pneumonias [17]. In children, studies corroborate an association between respiratory syncytial virus (RSV) and pneumococcus [18] with declines reported in RSV- and influenza-associated pneumonia hospitalisation rates following PCV introduction [19]. Viral and viral-bacterial co-infections are not uncommon in adults with pneumonia [20, 21]. In adults with pneumonia who tested RSV-positive, those who had a bacterial coinfection, were more likely to have a more severe outcome (longer length of hospitalisation and more frequent ICU admission) than those who had no coinfection [22].

In Mongolia in 2015, respiratory disease was amongst the five leading causes of hospitalisations in all age groups (345.6 per 10,000 population per year), with 44% of these admissions due to pneumonia. Respiratory disease was also amongst the top five causes of mortality (2.0 per 10,000 population) in the same year [23]. There is strong seasonal variation in pneumonia incidence [24], with the peak season occurring during the winter months (approximately October until April), exacerbated by extreme winter temperatures with high domestic coal use and resultant air pollution [25]. Published data from Mongolia document influenza burden [24] but data on the burden and severity of RSV in adults is more limited in the region [26].

The Mongolian Government introduced 13-valent PCV (PCV13) using a 2 + 1 infant schedule (age 2, 4 and 9 months) in a phased approach over 3 years from June 2016 starting with the capital city of Ulaanbaatar and ending with introduction into the provinces from April 2019. Enhanced hospital surveillance for paediatric pneumonia was initiated in four district hospitals and one tertiary hospital from April 2015 to monitor the direct impact of PCV13 introduction [27, 28]. Community carriage surveys in infants and toddlers showed a reduction in PCV13 serotypes 1 year post-introduction [29]. There are currently no data on the prevalent pneumococcal serotypes in adults in Mongolia.

The main aim of the current study is to evaluate the indirect impact of childhood PCV13 vaccination on adult pneumonia by establishing adult hospital surveillance in the same districts as the paediatric programme. This study will also allow us to determine the incidence of all cause pneumonia in Mongolia in adults 18 years and older, and to determine the changes in pneumococcal serotypes causing adult disease over time.

## Methods

### Study objectives

The primary study objective is to evaluate the association between childhood PCV13 introduction and the trends in incidence of severe clinical pneumonia (see case definition) in adults 18 years and older in four districts of Ulaanbaatar over a 7 year period (Jan 2015 – Mar 2022).

The study has multiple secondary objectives:
To evaluate the association between childhood PCV13 introduction and the trends in incidence of (a) clinical pneumonia or (b) hypoxic pneumonia only (see case definition) in adults 18 years and older in four districts of Ulaanbaatar over a 7 year period (Jan 2015 – Mar 2022).To evaluate the association between childhood PCV13 vaccination (during the early [2019–2020] and late [2021–2022] PCV13 introduction period) and the trends in adult pneumonia (see case definition) in four districts of Ulaanbaatar using the following endpoints: (a) all radiologically confirmed pneumonia, (b) definite pneumococcal pneumonia and (c) VT-pneumonia with a chest radiograph (CXR) consistent with CAP based on clinical assessment at time of hospitalisation.To evaluate the association between childhood PCV13 introduction (during the early and late PCV13 introduction period) and the trends in the detection and density of pneumococci in the nasopharynx of adults admitted with pneumonia.To assess changes in the detection of pneumococcal serotypes (VT and non-vaccine type [NVT]) associated with adult pneumonia in an era of ongoing childhood PCV vaccination.Among adults hospitalised for pneumonia, who have children of vaccine eligible age living in the household, to compare adult cases and controls with respect to having a child in the house who received one or more doses of PCV13 compared with households having all PCV13-unvaccinated children. The case-control comparison will be done for three subgroups: VT (case) compared with NVT pneumococcal pneumonia (control); end-point radiologically-confirmed pneumonia (case) compared with other radiologic findings (control); hypoxic (case) compared with non-hypoxic (control) pneumonia.To evaluate the association between PCV13 introduction in children on the trends in incidence and severity of adult pneumonia associated with viral pathogens (RSV or influenza) in four districts of Ulaanbaatar, during the early and late PCV13 introduction period, for the following endpoints: incidence of severe clinical pneumonia, clinical pneumonia, and radiologically confirmed pneumonia associated with RSV or influenza.

### Study setting

Mongolia has a well-structured health system with a clear referral pathway from primary family healthcare centres to secondary district hospitals, and finally tertiary hospitals for severe or complicated cases [30]. Most adults access public health care and most pneumonia cases are captured by the public health services in district and tertiary care facilities [23, 30, 31]. Hospital care is accessible with primary and secondary facilities in each district and payment is based on income. Private care and self-referral incur significant cost for individual patients.

Active hospital-based surveillance for adult pneumonia was established in 2019 in four district hospitals in four districts of Ulaanbaatar (Songinokhairkhan, Sükhbaatar, Bayanzürkh and Chingeltei). These are the same four districts with ongoing enhanced paediatric pneumonia surveillance. These four districts are the largest districts of Ulaanbaatar containing 70% of the population of Ulaanbaatar with a mixture of areas with formal and traditional informal (ger) housing. The vast majority of adult pneumonia cases in the four districts under study are expected to be captured by the surveillance programme [23, 30, 31]. Annual district-specific denominator data are available from the Mongolian National Statistics Office, allowing us to calculate incidence rates for our four study districts.

As part of the routine childhood immunisation schedule, two study districts had PCV13 introduced in June 2016 (Songinokhairkhan, Sükhbaatar), one district in July 2017 (Bayanzürkh) and the fourth district in March 2018 (Chingeltei). Catch-up campaigns, for children 12–23 months, with two PCV doses were instituted in 2016 and 2017, but not in 2018 [27]. There is currently no licensure or recommendations for adult pneumococcal vaccination in Mongolia, and the pneumococcal polysaccharide vaccine is not available in-country.

### Surveillance case definitions

#### Clinical pneumonia

Clinical pneumonia will be defined based on previously used case definitions [32]:

A diagnosis of pneumonia on admission, plus a discharge diagnosis of pneumonia, plus two or more of the following clinical signs and symptoms, at least one of which is respiratory:
subjective fever/chills or documented fever (≥38.0 °C)new cough or change in chronic coughnew or increased sputum productiondyspnoea or tachypnoea (i.e. difficult breathing or respiratory rate > 25 breaths/minute)lung findings on auscultation (rales, decreased breath sounds)leucocytosis (> 11.0 × 10^9^ cells/l) or leukopenia (< 4.0 × 10^9^ cells/l)SaO_2_ < 90% or respiratory distresspleuritic chest pain

#### Severe clinical pneumonia

Severe clinical pneumonia will be defined as clinical pneumonia with two or more severity signs: presence of confusion (Glasgow coma scale < 15), respiratory rate ≥ 30 breaths per minute, hypotension (systolic blood pressure ≤ 90 mmHg or diastolic blood pressure ≤ 60 mmHg) or hypoxaemia (oxygen saturation < 90%) [33]. All pneumonia patients who are admitted in the ICU, receive pressor support in ICU or who die will be considered to have severe disease [34, 35].

#### Hypoxic pneumonia

Hypoxic pneumonia will be defined as clinical pneumonia with an oxygen saturation of < 90% in room air on admission as measured by pulse oximeter.

#### Radiological pneumonia

An adapted version of the WHO definitions for radiological pneumonia in children [36], which accounts for underlying chronic lung disease and significant infiltrates, will be used to diagnose CXR-confirmed disease in adults. Currently, Pfizer is using data from a randomised controlled trial of PCV13 among adults aged ≥65 years in The Netherlands to assess whether the WHO criteria for end-point pneumonia in children are valid for predicting pneumococcal pneumonia in adults. Similar to the definitions used in previous adult pneumonia studies [32], the following three endpoints are proposed:
*Primary end-point pneumonia* will be defined as the presence of focal end-point consolidation (dense/fluffy opacity occupying portion/whole lobe or entire lung, that may or may not contain air-bronchograms) or pleural effusion in the lateral pleural space spatially associated with a pulmonary parenchymal infiltrate or if the effusion obliterated enough of the hemithorax to obscure an opacity.*Other infiltrates* will be defined as other patchy interstitial infiltrates without a pleural effusion or focal end-point consolidation. This will be a separate category as it may be difficult to confirm as acute lung disease in patients with a history of underlying chronic lung disease.*CXR-negative* will be defined as patients with no consolidation, infiltrate or effusion.

#### Definite pneumococcal pneumonia

Definite pneumococcal pneumonia will be defined as any clinical pneumonia admission with a positive blood or pleural fluid culture or a positive pneumococcal urine test from BinaxNOW® urinary antigen test; or any radiographically confirmed pneumonia (primary end-point pneumonia or any infiltrate consistent with CAP) with a positive multiplex SSUAD diagnostic assay result.

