#### Viral pneumonia co-infections

Pneumococcal viral co-infection will be defined as any clinical or radiological pneumonia case where both *S. pneumoniae* and RSV or influenza are detected in nasopharyngeal samples. *S. pneumoniae* will be identified by quantitative real-time polymerase chain reaction (PCR) targeting the *lytA* gene (qPCR) [37] and microarray as per testing algorithm [29]. RSV or influenza will be identified by RT-PCR [27]. In addition, for radiologically-confirmed pneumonia cases, pneumococcal viral co-infection will include cases with a positive pneumococcal urinary antigen test and RSV or influenza detected on nasopharyngeal sampling [27].

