##### Processing of other samples and CXRs

Any pleural fluid collected will be cultured and blood cultures will be taken according to standard clinical practice. Blood culturing practices may differ between the four hospitals and will not be done for all adult pneumonia cases. Pleural fluid will be tested by *lytA* qPCR in Mongolia if possible, otherwise shipped and tested at MCRI.

CXRs will be performed and archived for all pneumonia cases. CXRs will be digitalised and uploaded in an electronic database for re-reading according to adapted standardised WHO criteria. CXRs will be reread by two independent radiologists who are trained in WHO methodology, and results will be entered into the electronic database. Any disagreement in results between the two readers will be resolved by a third radiologist.

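### The definition of definite pneumococcal pneumonia leaves out the pleural fluid lytA qPCR that the study already plans, so a case shown to be pneumococcal only by that test is not counted

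*Protocol article*

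**What the plan says.** The section Definite pneumococcal pneumonia, under Surveillance case definitions, opens "Definite pneumococcal pneumonia will be defined as" and then gives two routes.

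- **Route 1:** "any clinical pneumonia admission with a positive blood or pleural fluid culture or a positive pneumococcal urine test", the urine test being BinaxNOW.
- **Route 2:** pneumonia confirmed on the radiograph (primary end-point pneumonia or an infiltrate consistent with CAP) "with a positive multiplex SSUAD diagnostic assay result".

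Nothing in the wording suggests that the list is only illustrative.

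The section Processing of other samples and CXRs describes the specimens. "Any pleural fluid collected will be cultured and blood cultures will be taken according to standard clinical practice". On coverage it says: "Blood culturing practices may differ between the four hospitals and will not be done for all adult pneumonia cases". On PCR it says: "Pleural fluid will be tested by *lytA* qPCR in Mongolia if possible, otherwise shipped and tested at MCRI".

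The section Viral pneumonia co-infections says of *S. pneumoniae* in nasopharyngeal samples that it "will be identified by quantitative real-time polymerase chain reaction (PCR) targeting the" lytA gene, together with microarray. So lytA qPCR is one of the study's own methods for identifying the organism.

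Under Study objectives, definite pneumococcal pneumonia is endpoint (b) of the secondary objective that follows trends between the early (2019–2020) and late (2021–2022) PCV13 introduction periods.

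**The concern.** The study will produce a pneumococcus-specific result from a normally sterile site, but its case definition makes no use of that result. A positive urine antigen test is enough on its own to make a case definite. Pneumococcal DNA in pleural fluid is not. Pleural culture can be negative when PCR is positive, for instance after antibiotics, and those are the patients for whom a PCR adds information.

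What is at stake is the completeness of one named secondary endpoint, which is to be compared over time. A definition that ignores a planned result also invites an improvised decision later: once pleural PCR results arrive, someone must decide whether they count, and the written rule says they do not. That is better settled before the early and late periods are compared.

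**Working it through.** No sample size, power or event figure in the article depends on this definition, so there is nothing to recompute. The check sets the definition beside the tests that are planned.

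**Step 1. List the pneumococcal tests planned for prospectively enrolled cases and see which ones count.**

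| Test | Where planned | Counts towards definite? |
|---|---|---|
| Blood culture | Processing of other samples and CXRs; standard practice, not all cases | Yes |
| Pleural fluid culture | Same section; whenever fluid is collected | Yes |
| BinaxNOW on urine | Urine processing; prospective cases | Yes |
| SSUAD on urine | Urine processing; 13 PCV13 serotypes + 11 further PPSV23 serotypes = 24 | Yes, if radiographically confirmed |
| lytA qPCR on pleural fluid | Processing of other samples and CXRs | **Not listed** |
| lytA qPCR and microarray on nasopharyngeal swab | Nasopharyngeal swab collection and testing | Not listed |

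Leaving out the nasopharyngeal result is reasonable, because a positive swab can reflect carriage. That reason does not carry over to pleural fluid.

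**Step 2. Write the rule out.** For a clinical pneumonia admission, let B, P and N be a positive blood culture, pleural culture and BinaxNOW test. Let U be a positive SSUAD result, R radiographic confirmation, and L a positive pleural lytA qPCR.

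- Rule as written: definite = B or P or N or (R and U).
- Rule with pleural PCR added: definite = B or P or N or (R and U) or L.

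**Step 3. Find the patients on whom the two rules differ.** They differ only where L is positive, B, P and N are each negative or not done, and R and U do not hold together. This is the whole of the affected group.

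**Step 4. Ask how a patient could be in that group.**

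- Pleural fluid must have been collected, which is not routine.
- Pleural culture must have failed. Blood culture must have failed or not been taken, and the article says it will not be taken for every case.
- BinaxNOW must be negative or missing. It targets an antigen common to all serotypes, so serotype alone does not rule out detection.
- SSUAD must be negative, missing or not qualifying. A serotype outside the 24 gives no positive result. The radiographic condition will seldom be the obstacle: the section Radiological pneumonia counts an effusion with an associated infiltrate, or one large enough to hide an opacity, as primary end-point pneumonia, and patients with fluid to sample are likely to meet that.

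**Step 5. Size.** A count would need the number of pleural samples, the PCR yield, and the joint failure rate of culture and both urine tests among PCR-positive patients. The article gives none of these, so no count can be derived. Step 4 suggests that it is small.

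**Step 6. Reach.** The calculation under Sample size estimation concerns severe clinical pneumonia, as does the primary model under Statistical analysis plan. Neither uses this definition. In the Nested case-control study, the vaccine-type versus non-vaccine-type comparison rests on the serotype-specific urine assays and is not affected either.

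**The case against.** The strongest reply is that the urine tests make the omission almost harmless. Urine is planned for prospectively enrolled cases, BinaxNOW is not limited by serotype, and SSUAD covers 24 serotypes. Most patients with pneumococcal empyema should reach the definition by one of these routes. This stands as an argument about size, and it means a reader should not infer that every culture-negative, PCR-positive patient is lost. It does not remove the gap, since a patient can still fail all of those routes while pleural PCR is positive.

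A second reply is that the article is condensed and the separate analysis plan may say what happens to the pleural PCR. It may. But the case definition is set out here in full, and as it stands it excludes the result.

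A reader might also infer something stronger from the culture criterion. It names no organism, and the word pneumococcal is attached only to the urine test, so on a literal reading any bacterial growth or contaminant would make a case definite. The article does not support that inference. The sentence defines a term with pneumococcal in its name, so a culture positive for pneumococcus is the natural meaning. The SSUAD criterion likewise does not repeat the word, and no one would misread it. Nothing shows that non-pneumococcal cultures will be counted, and no estimate of false cases should be attached to this wording. Naming the organism is a clarification only.

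Finally, differences in blood culturing between hospitals might be cited as making the problem worse. They affect correctly identified pneumococcal cultures too. The article already discloses them, and rewording the definition would not remove them.

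**Conclusion.** The point holds in a narrow form. The definition omits a pneumococcus-specific test on pleural fluid that the same article plans to run, and no other section gives the result a use. A patient whose only positive pneumococcal evidence is pleural PCR is therefore left out of secondary endpoint (b).

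This is a minor point. The affected group is limited to patients with pleural fluid collected whose cultures, BinaxNOW and qualifying SSUAD are all negative or not done. It is probably small, and the article gives no rates from which to count it. That judgement assumes urine is collected and tested as planned; if urine were often missing in patients with effusions, the group would be larger. The primary endpoint, its model and the power statement do not depend on this definition. The article does not show that the definition admits non-pneumococcal cases.

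**What to change.** Rewrite the first route so that it covers a clinical pneumonia admission with any one of:

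- blood or pleural fluid culture positive for *S. pneumoniae*;
- pleural fluid positive for *S. pneumoniae* by lytA qPCR;
- a positive BinaxNOW urine test.

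Leave the SSUAD route as it is. The second item is the substantive change. Naming the organism in the first only makes the evident intent explicit. If pleural PCR was left out on purpose, say so and give the reason.

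The cost is one sentence in the case definition and the matching line in the analysis plan and endpoint derivation. No extra specimen, assay or visit is needed, because the pleural PCR is already planned. The change should be made before the early and late periods are compared on this endpoint.

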##### Urine processing

Urine samples from adult cases enrolled prospectively in the adult surveillance programme, will be tested at the NCCD bacteriology laboratory in Mongolia using a rapid pneumococcal urinary antigen test (BinaxNOW®, Alere North America, Orlando, Florida). The BinaxNOW® *Streptococcus pneumoniae* test is an immunochromatographic membrane assay test used to detect pneumococcal soluble antigen in human urine. It detects the pneumococcal C-polysaccharide which is found in the cell wall and is common to all serotypes. BinaxNOW® urine testing conducted at the NCCD bacteriology laboratory will be conducted by two designated trained laboratory technicians according to study standard operating procedures to ensure consistency of results.

Additional urine will be frozen in ultra-low temperature (− 70 °C) freezers before being shipped to the Pfizer Laboratories, Pearl River, USA for pneumococcal testing using multiplex SSUAD assays that assesses the 13 serotypes in PCV13 (UAD1) [4] and the additional 11 serotypes in 23-valent pneumococcal polysaccharide vaccine (PPSV23) (UAD2) [3]. Positivity cut-off limits for the SSUAD assay will be established based on antigen concentrations read off a standard curve for each serotype using the 400 urine specimens collected from control subjects as described above. While UAD cut-points have only rarely been reset based on evaluation of local healthy control subjects, this step ensures test validity and high specificity.

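### The definite pneumococcal pneumonia endpoint is more sensitive for the 24 serotypes covered by SSUAD than for the rest, so replacement by types outside the 24 could exaggerate a fall in its trend

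*Protocol article*

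**What the plan says.** The section Definite pneumococcal pneumonia gives three ways into the endpoint. Two are open to every clinical pneumonia case: a positive BinaxNOW urine test, or a positive culture ("any clinical pneumonia admission with a positive blood or pleural fluid culture"). The third is SSUAD, which counts only with a radiographic finding: "any radiographically confirmed pneumonia (primary end-point pneumonia or any infiltrate consistent with CAP) with a positive multiplex SSUAD diagnostic assay result".

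Urine processing gives the serotype reach of the urine tests. The first SSUAD panel is described as "multiplex SSUAD assays that assesses the 13 serotypes in PCV13 (UAD1"), and the second adds "the additional 11 serotypes in 23-valent pneumococcal polysaccharide vaccine (PPSV23) (UAD2"). Of BinaxNOW it says: "It detects the pneumococcal C-polysaccharide which is found in the cell wall and is common to all serotypes". On culture, Processing of other samples and CXRs says: "Blood culturing practices may differ between the four hospitals and will not be done for all adult pneumonia cases".

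In Study objectives, the second secondary objective evaluates the association between childhood PCV13 vaccination and adult pneumonia trends in the early (2019–2020) and late (2021–2022) periods. One of its endpoints is "b) definite pneumococcal pneumonia". The Statistical analysis plan section states that no urine data exist from before PCV13, so this endpoint is followed only after introduction. The Background says of carriage that "overall pneumococcal carriage prevalence is only slightly decreased (or unchanged) due to serotype replacement".

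**The concern.** As a description of burden, the composite is sensible: every available test that can confirm pneumococcus is used. A trend makes a further demand, namely that the chance of detecting a true case stays the same over the period compared. Here that chance depends on serotype, and it is higher for a group that contains every PCV13 type. If the serotype mix moves from the 24 towards other types between 2019–2020 and 2021–2022, the proportion of true pneumococcal cases that are detected falls, and the endpoint falls with it even if true disease does not.

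The error would run towards a vaccine benefit, in an endpoint meant to measure the association with PCV13. There is no urine baseline from before PCV13 against which to judge it, and the article describes no adjustment for unequal serotype coverage.

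**Working it through.** The protocol states no sensitivity, power or expected count for this endpoint. Its 92% power is for severe clinical pneumonia, which does not use this definition. There is thus no figure to reproduce, and the check below is illustrative.

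**From the protocol.** SSUAD covers 13 + 11 = 24 serotypes. BinaxNOW and culture are not limited by serotype. SSUAD counts only in radiographically confirmed cases.

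**Assumed (none of these is in the protocol).**
- True pneumococcal incidence is constant, and half of PCV13-type disease is replaced.
- Sensitivities of BinaxNOW (sB) and SSUAD (sU): 0.80 and 0.80, 0.65 and 0.90, or 0.50 and 0.95, each equal across the serotypes that the test covers.
- Culture yield c: 0 or 0.1. Radiographically confirmed share r: 1 or 0.6.
- Starting mix of PCV13 types / the 11 others / outside the 24: 50/25/25 or 30/40/30.
- Tests independent or nested (the poorer test finds only cases that the better one also finds).

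This gives 3 × 2 × 2 × 2 × 2 = 48 scenarios.

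**Formulas.**
- Outside the 24: S_out = 1 − (1 − sB)(1 − c)
- Within the 24, all tests counting: S_both = 1 − (1 − sB)(1 − c)(1 − sU) if independent; max(S_out, sU) if nested
- Within the 24 overall: S_24 = r × S_both + (1 − r) × S_out
- Detected at the start: D = (p13 + p11) × S_24 + p_out × S_out
- Apparent change = −(1 − q) × 0.5 × p13 × (S_24 − S_out) / D, where q is the share of replacement going to the 11 additional types

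**Largest effect** (50/25/25, sB 0.50, sU 0.95, c = 0, r = 1, independent).
- S_out = 0.500; S_24 = 1 − 0.5 × 0.05 = 0.975
- D = 0.75 × 0.975 + 0.25 × 0.500 = 0.856
- All replacement outside the 24 (q = 0): −0.25 × 0.475 / 0.856 = −13.9%
- Half outside (q = 0.5): −6.9%

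**A middle case** (50/25/25, sB 0.65, sU 0.90, c = 0.1, r = 0.6, independent).
- S_out = 1 − 0.35 × 0.9 = 0.685; S_both = 1 − 0.35 × 0.9 × 0.1 = 0.969
- S_24 = 0.6 × 0.969 + 0.4 × 0.685 = 0.855
- D = 0.75 × 0.855 + 0.25 × 0.685 = 0.813
- q = 0: −0.25 × 0.170 / 0.813 = −5.2%; q = 0.5: −2.6%

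**No effect** (sB = sU = 0.80, nested). SSUAD adds nothing, S_24 = S_out, and the change is 0%.

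| Replacement outside the 24 | Apparent change over the 48 scenarios |
|---|---|
| None (all by the 11 additional types) | 0% in every scenario |
| Half | 0 to −6.9% |
| All | 0 to −13.9% |

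The sign does not depend on the assumed values. S_24 cannot be below S_out, because SSUAD only adds positives, so a shift out of the 24 gives a fall or no change. An endpoint built on BinaxNOW or culture alone has sensitivity S_out for every serotype in this model, so its apparent change is 0% throughout.

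**The case against.** A reader might infer that types outside the 24 are detected by BinaxNOW only, and that any serotype replacement after PCV13 would show up as a fall in pneumococcal pneumonia. The protocol supports neither. Blood and pleural fluid culture also count and are not tied to serotype, although incomplete culturing limits what they recover. The 11 additional types are all non-PCV13 types and enter by the same routes as the PCV13 types, so replacement by them leaves no artefact. Even for types outside the 24, BinaxNOW and culture still find a share.

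Other points also narrow the concern. The Background sentence on replacement is about carriage, and the next sentence says that vaccine types tend to cause disease more readily than their replacements; full replacement in disease is therefore a stress test, not what the protocol predicts. All four districts had introduced PCV13 by March 2018, and carriage of its types in young children had fallen within a year of introduction, so part of any shift may precede 2019. The vaccine-type endpoint, the serotype comparison of year one with year three, and nasopharyngeal microarray would all help in reading the trend. A separate analysis plan exists and may contain a sensitivity analysis.

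These arguments limit the size; they do not remove the mechanism. Urine testing cannot name a type outside the 24, and microarray describes carriage and is not part of the endpoint. The companion analyses can hint at replacement but do not correct this trend. The definition and its use as a trend endpoint are both fixed in the article, so the point does not rest on a detail left to the analysis plan.

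**Conclusion.** The concern holds in limited form. In radiographically confirmed cases the composite favours the 24 SSUAD types, and replacement by types outside them during 2019–2022 would exaggerate any fall in this endpoint. The direction follows from the definition, provided SSUAD finds some cases that the other tests miss. The size does not: it rests wholly on assumed sensitivities, serotype shares and replacement, and it can be zero. The stress test gives 0 to about −7% with half of the replacement outside the 24, and 0 to about −14% with all of it outside. The protocol itself notes that no data exist on adult serotypes in Mongolia, so the range cannot be tightened from the document.

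It would be wrong to conclude that an observed fall must be an artefact, or that the composite is unfit for describing burden. One endpoint of one secondary objective is affected; the primary endpoint is clinical and does not use these tests.

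**What to change.** Keep the composite as defined, and pre-specify three additions for this endpoint:

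1. The same trend on the serotype-independent tests already in the definition: BinaxNOW, or blood or pleural fluid culture.
2. A yearly table of BinaxNOW-positive, SSUAD-negative cases among those tested with both. This is the main urine signal of types outside the 24, though it also includes SSUAD misses within the 24.
3. A rule of interpretation: a fall in the composite is attributed to less pneumococcal pneumonia only if the serotype-independent trend agrees.

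No new sample or test is needed, only wording in the analysis plan. The cost is precision. In the scenarios above, positives drop from D to S_out: none are lost where SSUAD adds nothing, 1 − 0.685/0.813 = 16% in the middle case, and 1 − 0.500/0.856 = 42% in the largest. This is why the second trend should stand beside the composite and not replace it. Culture practice differs between hospitals, and any change in it over time would affect both trends.
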